## **6.3 Study procedures**

All diagnostic and other procedures are outlined in appendix C, a distinction is made between common clinical practice and extra procedures patients will undergo if they choose to participate in this study.

Subjects will be evaluated for clinical stability every day of hospitalization. Laboratory evaluations will be performed for hospitalised patients at day 1 and days 3-7 until the threshold level is reached. Any laboratory evaluation after day 7 will be on indication. Microbiological evaluations will be determined at baseline and if applicable on day 30. An outpatient visit will be scheduled at day 30. A detailed overview of the different procedures is outlined below.

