## **3. Study design**

This study will be set up as a Randomised Controlled Trial with a parallel design, patients will be randomly allocated to one of 3 treatment groups. No blinding will be performed, since treating physicians will have to make a decision to continue or withhold treatment based on laboratory evaluations. In order to make the right decision they will have to know whether or not the patient is receiving antibiotics.

Patients will be included at hospital admission and the follow up period is 1 month. The control group will consist of patients getting treated according to common clinical practice.

Patients will be admitted to hospital and receive therapy according to the study protocol. They will be discharged from the hospital when their medical condition and social situation is stable. If patients are discharged and still using antibiotics, blood tests will be performed daily in the participating centre and the researcher will contact the patients by phone to inform them whether or not antibiotic treatment can be discontinued. After discharge the patient will be evaluated at an outpatient visit on day 30. In case of any event an interim visit will be scheduled. If for some reason a patient fails to perform an outpatient blood test, antibiotics will be continued until the next blood test or for a total of 7 days and the reason for failure will be documented.

This study will be conducted in the Medical Centre Alkmaar, the Isala clinics in Zwolle and the Slotervaart hospital in Amsterdam.

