### **5.3 Days 4 and after – PCT guided group**

Each day a blood test will be performed assessing the PCT level in the blood. If this shows a procalcitonin level below 0.25 mcg/L **or** a reduction to 10% of the initial value treatment will be discontinued. After the decision to discontinue treatment is made no further blood tests will be performed unless the patient has worsening symptoms.

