#### **6.4.2 Days 2 and 3**

1. Vital signs (pulse, respiration rate, heart rate, blood pressure, and body temperature, Oxygen Saturation) will be recorded three times a day. Each day time to clinical stability will be assessed.
2. Laboratory examination: on indication.
3. Clinical improvement/failure is scored according to Chow et al (appendix B). If treatment needs to be changed because the subjects fails to improve clinically then the subject should be evaluated as a treatment failure and appropriate therapy instituted. This therapy should be recorded.
4. If possible patients will be switched from iv therapy to oral therapy. It is appropriate to switch to oral medication in the following situations: 
  - a. Hemodynamically stable
  - b. If respiratory symptoms such as cough, fever, shortness of breath, and chest pain are improving.
  - c. Oral intake and gastrointestinal absorption adequate.

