#### **6.4.3 Days 4-7**

1. Vital signs (pulse, respiration rate, heart rate, blood pressure, and body temperature, Oxygen Saturation) will be recorded three times a day if the patient is still admitted to hospital.

2. Laboratory examination: CRP, PCT, WBC and on indication other tests will be performed until the patient is discharged.
3. Clinical improvement/failure is scored according to Chow et al (appendix B). If treatment needs to be changed because the subjects fails to improve clinically then the subject should be evaluated as a treatment failure and appropriate therapy instituted. This therapy should be recorded.
4. If possible patients will be switched from iv therapy to oral therapy. It is appropriate to switch to oral medication in the following situations:
  - a. Oral temperature or equivalent <37.8 °C (100.3 °F) for at least 24 hours.
  - b. If respiratory symptoms such as cough, shortness of breath, and chest pain are improving.
  - c. Oral intake and gastrointestinal absorption adequate.
  - d. White blood cell count normalizing.
5. Patients may be discharged from the hospital if they meet the following criteria:
  - a. No longer require iv medication, criteria for switching from iv to oral medication mentioned above.
  - b. If their clinical and social situation is stable.
    - i. Clinical stability is defined as:
      1. Temperature <37.8 °C (100.3 °F)
      2. Heart rate <100 beats/min
      3. Respiratory rate < 24 breaths/minute
      4. Systolic blood pressure > 90 mm Hg
      5. Arterial oxygen saturation >90% or pO2 >60 mm Hg on room air
      6. Ability to maintain oral intake
      7. Normal mental status
6. Treatment may be discontinued in the CRP group if the patient shows clinical improvement and the CRP is below 100 mg/L **and** shows a reduction to 50% of the initial value.
7. Treatment may be discontinued in the PCT group if the patient shows clinical improvement and the PCT level is below 0.25 mcg/L **or** shows a reduction to 10% of the initial value.

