## Appendix C: List of study procedures

|                     | Day 1 |   | Day 2 |   | Day 3 |   | Day 4 |   | Day 5 |   | Day 6 |   | Day 7 |   | Day 30 |   |
|---------------------|-------|---|-------|---|-------|---|-------|---|-------|---|-------|---|-------|---|--------|---|
|                     | R     | E | R     | E | R     | E | R     | E | R     | E | R     | E | R     | E | R      | E |
| Blood tests         | X     | X |       |   |       |   |       |   |       | X |       | X |       | X |        | X |
| X-ray               | X     |   |       |   |       |   | X     |   |       |   |       |   |       |   | X      |   |
| Sputum sample       | X     |   |       |   |       |   |       |   |       |   |       |   |       |   |        | X |
| Blood culture       | X     |   |       |   |       |   |       |   |       |   |       |   |       |   |        |   |
| Nasopharyngeal swab |       | X |       |   |       |   |       |   |       |   |       |   |       |   |        |   |
|                     |       |   |       |   |       |   |       |   |       |   |       |   |       |   |        |   |
|                     |       |   |       |   |       |   |       |   |       |   |       |   |       |   |        |   |
|                     |       |   |       |   |       |   |       |   |       |   |       |   |       |   |        |   |

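### The biomarker test days and the stopping rule contradict each other across sections 2.1, 3, 5.3, 5.4, 6.3, 6.4 and the appendices, and they determine the primary endpoint

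*Protocol*

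**What the plan says.** **First test after baseline**
- Section 6.3: "Laboratory evaluations will be performed for hospitalised patients at day 1 and days 3-7 until the threshold level is reached". Day 3 is a scheduled test day.
- Section 6.4.2, for days 2 and 3: "Laboratory examination: on indication".
- Section 5.3, headed for day 4 onward: "Each day a blood test will be performed assessing the PCT level in the blood". Section 5.4 says the same for CRP, and 6.4.3 also starts at day 4.
- Appendix C, as it can be read here, marks blood tests on days 1, 5, 6, 7 and 30.

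**Last test**
- Section 6.3: "Any laboratory evaluation after day 7 will be on indication".
- Sections 5.3 and 5.4: daily until the decision to stop, with no end day.
- Section 6.4.3: "Laboratory examination: CRP, PCT, WBC and on indication other tests will be performed until the patient is discharged".
- Section 3: "If patients are discharged and still using antibiotics, blood tests will be performed daily in the participating centre".

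**Stopping rule**
- Sections 2.1, 5.3 and 5.4: antibiotics *will* be stopped once the marker criterion is met; no other condition is named.
- Section 6.4.3: "Treatment may be discontinued in the PCT group if the patient shows clinical improvement and the PCT level is below 0.25 mcg/L", or has fallen to 10% of its initial value. The CRP item has the same form.
- Appendix A (in Dutch): treatment is not stopped if the treating physician thinks that unsafe.

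The numerical thresholds are the same throughout. Only the test days and the force of the rule differ.

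**The concern.** The intervention in the two biomarker arms is a test-and-stop rule, and the primary endpoint is the duration of antibiotic treatment. The day a test is scheduled, and whether its result binds, therefore feed straight into the endpoint. A patient who meets the marker criterion without clinical improvement must stop under 5.3 or 5.4, but does not meet the stopping condition in 6.4.3. A patient in hospital and above threshold after day 7 is tested daily under 5.3 or 5.4, and only on indication under 6.3.

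The per-protocol population is affected too. Section 8.3.2 admits patients treated as the protocol lays down and excludes those whose medication ended before the planned time. With two stopping rules and several schedules, the same course can be adherent under one section and a deviation under another.

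**Working it through.** **1. The plan's own figure.** Section 8.1 gives 139 per group (146 if not normal), using a 2-day difference, alpha 0.025 and power 0.80. With the PCT and control SDs, the pooled SD is √((4.80257² + 5.87499²)/2) = 5.366. A two-sided two-sample t test (noncentral t) has power 0.7997 at 138 per group and 0.8029 at 139, so n = 139. Dividing by the Mann-Whitney efficiency 3/π gives 139 × π/3 = 145.6, or 146. Both figures reproduce.

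**2. Passages side by side**

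| Question | Answers given |
|---|---|
| First test after day 1 | Day 3 (6.3); on indication on days 2 and 3 (6.4.2); day 4 (5.3, 5.4, 6.4.3); day 5 (Appendix C as read here) |
| Test after day 7 | On indication (6.3); daily, no end (5.3, 5.4); daily after discharge while on antibiotics (3) |
| Effect of meeting the threshold | Stop (2.1, 5.3, 5.4); may stop, if clinically improving (6.4.3); not if the physician thinks it unsafe (Appendix A) |

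No section says what happens to a patient still above threshold after day 7 if 6.3 is followed. The 7-day fallback in section 3 covers a missed outpatient test only.

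**3. How many planning cases lie beyond day 7.** Inputs from section 8.1: PCT n 173, mean 6.2832, SD 4.80257; CRP n 196, mean 5.1327, SD 3.61518; range 1 to 14 in both. Write X for duration. E[X²] = mean² + SD² × (n − 1)/n.
- PCT: 39.4786 + 23.0647 × 172/173 = 62.410
- CRP: 26.3446 + 13.0695 × 195/196 = 39.347

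On 1 to 14, (X − 1)(X − 7)/91 is at most 0 up to day 7 and at most 1 after it. Its mean is therefore a lower bound on the share above 7 days, (E[X²] − 8 × mean + 7)/91:
- PCT: (62.410 − 50.266 + 7)/91 = 0.210, at least 21%
- CRP: (39.347 − 41.062 + 7)/91 = 0.058, about 6%

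The matching upper bound for whole days, 1 − (E[X²] − 22 × mean + 112)/91, is 60% (PCT) and 58% (CRP).

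**4. Moving the earliest stop from day 4 to day 5.** With whole-day durations, only cases of 4 days or fewer move, each by one day, so the shift in the mean equals their share.
- Lower bound, (E[X²] − 19 × mean + 70)/52. PCT: 13.029/52 = 0.25. CRP: 11.826/52 = 0.23.
- Upper bound, 1 − (E[X²] − 5 × mean + 4)/130. PCT: 1 − 34.994/130 = 0.73. CRP: 1 − 17.684/130 = 0.86.

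The target difference is 2 days.

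**The case against.** Several points on the other side stand.

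- **Part of the text is complementary.** Section 6.3 speaks of hospitalised patients and 6.4.3 runs to discharge, while section 3 covers patients discharged on antibiotics. A reader might infer that late patients have no scheduled test at all. Sections 3, 5.3 and 5.4 do schedule one, so this is a conflict with 6.3, not an absence.
- **No section gives a day-3 stop.** Section 5.1 treats everyone for 3 days, and the stopping rules in sections 5 and 6 sit under headings that begin at day 4. Day 3 is a test day in 6.3, no more. A spread of stop days from day 3 to day 5 is not supported.
- **Day 5 rests on one table.** Appendix C may have shifted columns: its last blood-test mark falls on day 30, where 6.4.5 leaves laboratory tests to indication. Without it, the conflict over the first test is day 3 against day 4.
- **A day-5 first test would not rule out a 2-day difference.** That inference takes the control mean as exactly 7 days. The planning control mean is 8.76, and 5.2 allows lengthening.
- **Control-arm contamination is not shown to shrink the contrast.** Section 6.4.3 orders both markers without limit by arm, but 5.2 lets physicians only lengthen control treatment, which would widen the difference.
- **Allocation is balanced within centres.** Blocks are assigned to centres at 1:1:1, so different readings by centre do not themselves bias the randomised comparison. They make the estimate an average over different interventions.
- **The stopping wording can be read together.** Section 6.4.3 is part of the detailed overview and agrees in spirit with Appendix A, which suggests that the marker was not meant to bind alone. That is a plausible reading, but 2.1, 5.3 and 5.4 say otherwise, and a centre should not have to guess.

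**Conclusion.** The point holds as an internal contradiction in the definition of the intervention. Three conflicts stand on the text alone: whether day 3 is a scheduled test, whether testing continues after day 7, and whether the marker result binds or is conditional on clinical improvement. A fourth, the day-5 start in Appendix C, must be checked against the original table.

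The conflict after day 7 concerns at least 21% of PCT and 6% of CRP planning cases. These are bounds on theoretical durations taken retrospectively from another trial's database, with a minimum of 1 day; they are not forecasts under a 3-day minimum. The shift of 0.25 to 0.73 days (PCT) or 0.23 to 0.86 days (CRP) assumes whole-day durations, an earliest stop on the day of the first test, and Appendix C as read here. The effect of missing tests after day 7 cannot be computed, because no rule is given for those patients. The sample size calculation is unaffected.

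This should be corrected before the protocol is used, because it concerns what is delivered in both experimental arms and how adherence is judged.

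**What to change.** Reconcile sections 2.1, 3, 5.3, 5.4, 6.3, 6.4.2, 6.4.3, Appendix A and Appendix C so that they state:
- one test schedule: first and last test day, in and out of hospital, and what applies if the threshold is not met at the last scheduled test;
- one stopping rule: whether the marker result binds or is conditional on clinical improvement, and where the treating physician's judgement enters;
- which markers are measured in which arm, so that 6.4.3 agrees with 5.3 and 5.4.

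Check the blood-test row of Appendix C against the original table. Then define adherence in section 8.3.2 by reference to the single rule. Which schedule and rule apply is for the investigators to decide. The cost is amendment text and a corrected Appendix C; no change to the sample size follows from this point.

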### **5.4 Days 4 and after – CRP guided group**

Each day a blood test will be performed assessing the CRP level in the blood. If this shows a CRP below 100 mg/L **and** a reduction to 50% of the initial value treatment will be discontinued. After the decision to discontinue treatment is made no further blood tests will be performed unless the patient has worsening symptoms.

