## **8. Data analysis**

### **8.1 Calculation of study numbers**

The objective of this study is to assess the efficacy of two different treatment regimens as compared to current general practice. The primary analysis will be the comparison of the duration of antibiotic

treatment of the CRP-guided treatment group compared to common practice and of the PCT-guided treatment group compared to common practice in the intent-to-treat (ITT) population. A per-protocol analysis will be performed as well.

We used the criteria mentioned above for CRP and PCT (procalcitonin level below 0.25 mcg/L **or** a reduction to 10% of the initial value; CRP below 100 mg/L **and** a reduction to 50% of the initial value) to retrospectively perform an analysis on the database from the CAPISCE trial to predict a mean and a standard deviation of antibiotic treatment for both groups in order to perform the power analysis. We then retrospectively selected 170 cases from the CAP-START trial to derive a mean and standard deviation for the common clinical practice group. The results of all groups are listed below:

| Duration of theoretical antibiotic treatment in the CRP guided group |     |         |         |        |                |
|-----------------------------------------------------------------------------|-----|---------|---------|--------|----------------|
|                                                                             | N   | Minimum | Maximum | Mean   | Std. Deviation |
| crpdag                                                                      | 196 | 1,00    | 14,00   | 5,1327 | 3,61518        |

| Duration of theoretical antibiotic treatment in the PCT guided group |     |         |         |        |                |
|-----------------------------------------------------------------------------|-----|---------|---------|--------|----------------|
|                                                                             | N   | Minimum | Maximum | Mean   | Std. Deviation |
| pctdag                                                                      | 173 | 1,00    | 14,00   | 6,2832 | 4,80257        |

| Duration of antibiotic treatment in the Common Clinical Practice group |     |         |         |        |                |
|-------------------------------------------------------------------------------|-----|---------|---------|--------|----------------|

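### After day 7 the protocol gives guided patients two conflicting testing schedules: daily PCT or CRP until the stop rule is met (3, 5.3, 5.4), or tests only on indication (6.3, Appendix C)

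*Protocol*

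**What the plan says.** **Testing continues until the rule is met.** Protocol 5.3 and 5.4 both cover day 4 onwards. For the PCT arm: "Each day a blood test will be performed assessing the PCT level in the blood". For the CRP arm: "Each day a blood test will be performed assessing the CRP level in the blood". Both end testing once the decision to stop has been made; neither names a last calendar day. Section 3 adds, for outpatients: "If patients are discharged and still using antibiotics, blood tests will be performed daily in the participating centre".

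**Testing is scheduled to day 7 only.** Section 6.3 states: "Laboratory evaluations will be performed for hospitalised patients at day 1 and days 3-7 until the threshold level is reached". It then adds: "Any laboratory evaluation after day 7 will be on indication". Section 6.4.3 sets out the stop rules in a section limited to days 4 to 7, for example "Treatment may be discontinued in the PCT group if the patient shows clinical improvement" together with the PCT criterion. The Appendix C columns go from day 7 directly to day 30.

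**Default for a missed test.** Section 3 says that if an outpatient test is missed, "antibiotics will be continued until the next blood test or for a total of 7 days".

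**Planning data.** Sections 4.4 and 8.1 tabulate theoretical rule-based durations from an earlier trial's database. Both guided tables have a maximum of 14 days. The PCT row, in the order N, minimum, maximum, mean, SD, reads "173 | 1,00 | 14,00 | 6,2832 | 4,80257".

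The index lists a section 6.4.4 for day 14 whose body is not in the text available. It is not treated as missing, and statements here about what the protocol leaves open are subject to it.

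**The concern.** The guided strategies work only if the marker is measured. For a guided patient above threshold on day 7, sections 3, 5.3 and 5.4 call for a test on day 8, while 6.3 and Appendix C schedule none. If a centre follows 6.3, the protocol text at hand does not say how long antibiotics continue without a value. The missed-test default does not help, because its 7-day limit has already been reached.

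The patients affected are the slow responders, who supply the long courses in the guided arms and so carry much weight in mean duration. The trial is unblinded and runs in three centres, each of which could follow a different section. Part of any difference in duration could then reflect the testing schedule and not the marker rule. Anyone stopped untested while still above threshold would bear on the safety half of the primary objective and on relapse and clinical response. This is a treatment instruction, so the analysis cannot repair it afterwards.

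**Working it through.** **1. The plan's own figure.** Pooled SD for PCT and control: √((5.87499² + 4.80257²)/2) = 5.3656. With a 2-day difference, two-sided alpha 0.025 and power 0.80, the normal approximation gives n = 2 × (2.2414 + 0.8416)² × 5.3656² / 2² ≈ 137 per group. The exact t calculation gives 139. Dividing by the Mann-Whitney efficiency 0.955 gives 145.5, so 146. The stated 139 and 146 are reproduced.

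**2. Moments of the planning tables (4.4 and 8.1).**

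| | N | Mean | SD | Sum of days | Sum of squares | Mean square |
|---|---|---|---|---|---|---|
| PCT | 173 | 6.2832 | 4.80257 | 1087 | 172 × 4.80257² + 1087²/173 = 10797 | 62.410 |
| CRP | 196 | 5.1327 | 3.61518 | 1006 | 195 × 3.61518² + 1006²/196 = 7712 | 39.347 |

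**3. Smallest possible share beyond day 7.** For a duration x between 1 and 14, the function (x − 1)(x − 7)/91 is at most 0 when x ≤ 7 and at most 1 when x > 7. Its mean therefore cannot exceed the share with x > 7:

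share ≥ (mean square − 8 × mean + 7)/91

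- PCT: (62.410 − 50.266 + 7)/91 = 19.144/91 = 0.2104. Then 0.2104 × 173 = 36.4, so at least 37 cases (21%).
- CRP: (39.347 − 41.061 + 7)/91 = 5.286/91 = 0.0581. Then 0.0581 × 196 = 11.4, so at least 12 cases (6%).

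A linear programme over whole days 1 to 14, with N, mean and SD fixed and at least one case at each end, gives the same minima. Its maxima are 60% (PCT) and 58% (CRP).

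**4. Worst-case shift if all courses were cut at day 7.** The shift is the mean of max(x − 7, 0). Since (x − 1)(x − 7)/13 never exceeds max(x − 7, 0) on 1 to 14, the lower limits are:

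- PCT: 19.144/13 = 1.47 days
- CRP: 5.286/13 = 0.41 days

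The upper limits from the linear programme are 2.05 days (PCT) and 1.09 days (CRP). The PCT planning mean would fall from 6.28 to between 4.23 and 4.81, and the CRP mean from 5.13 to between 4.04 and 4.73. The 3-day minimum of section 5.1 changes only values below 3, so it leaves these shifts as they are.

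**5. Sensitivity to day counting.** If the planning variable were offset by one, so that the cut falls beyond day 8, the bound becomes (mean square − 9 × mean + 8)/78. That is 13.861/78 = 17.8% for PCT and 1.153/78 = 1.5% for CRP. The size of the problem rests mainly on PCT.

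**The case against.** The strongest reply is that the sections can be reconciled. Section 6.3 is a short summary of laboratory work for all arms, and a guided patient still on antibiotics, whose strategy needs a marker value, arguably has an indication for a test. Section 2.1 ties extension of treatment to the marker, and section 3 separately orders daily outpatient tests. This is a reasonable guess at the intent. But 6.3 contrasts tests on indication with scheduled ones and does not say that remaining on antibiotics is an indication. The ambiguity stands, and one sentence would remove it.

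Four stronger readings are tempting, and the documents support none of them:

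- *Guided patients are stopped at day 7.* No section orders this. Section 6.3 concerns tests, not antibiotic duration, and the only 7-day default in the guided arms is for a missed outpatient test. The shift in step 4 is therefore a worst case, not a forecast. If antibiotics instead continued untested, the documents give no figure.
- *At least 21% of the trial's PCT patients are affected.* The bound describes 173 retrospective, theoretical durations from another trial. It carries over only if patients are similar.
- *The planning tables assume daily testing to day 14.* They give 14 only as a maximum. It may be an observed stop day, a cap or a code for never meeting the rule.
- *The tables show how far the between-arm difference moves.* Subtracting tabulated means gives 8.76 − 6.28 = 2.48 days for PCT, but the tables (minimum 1 day) do not apply the protocol's 3-day minimum. With that floor the uncapped PCT difference could lie anywhere from 1.58 to 2.46 days, so 2.48 does not describe treatment under 5.3.

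**Conclusion.** The conflict is in the current text and concerns the measurement that determines the primary outcome. A guided patient above threshold on day 7 is to be tested daily under 3, 5.3 and 5.4, and only on indication under 6.3. Such patients are not rare in the protocol's own planning data. The PCT minimum of 21% needs only the tabulated N, mean, SD and range; applying it to the trial requires similar patients and the same day count.

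The worst-case PCT shift is about as large as the 2-day relevant difference, but it arises only if centres stop treatment for lack of a test, which nothing instructs them to do. The finding is that the protocol leaves room for this, not that it will happen. The required 139 and 146 per group are not in question. The change should be made.

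**What to change.** Replace the last-day sentence in 6.3 with: *After day 7, PCT or CRP is measured daily in guided patients still on antibiotics, in hospital or after discharge, until the stop rule is met; other laboratory tests are on indication.* Carry the same rule into 6.4.3, so that the stop criteria are not confined to days 4 to 7, and add the period after day 7 to Appendix C.

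Two details should be settled at the same time:

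- If a last test day is wanted, such as day 14, state that antibiotics beyond it are at the physician's decision with the reason recorded. Otherwise the gap at day 7 is only moved to day 14.
- State the default when a test is missed after day 7, since the rule in section 3 gives none.

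The cost is wording in a few places. With a day-14 limit it adds at most seven samples (days 8 to 14) per guided patient still on antibiotics, which 3, 5.3 and 5.4 already imply. The sample size is unchanged.
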